## Abstract

**Methods and analysis::**

The objective of this study is to compare the effects of PBM with a light-emitting diode mask (660 nm, 6.4 mW/ cm², 8,02 J/ cm², 5.02 mW, 21 minutes) on facial rejuvenation using 2 frequency applications for 4 weeks: one group will receive PBM application on the face, twice a week and another group will receive PBM application 3 times a week. A group with simulated PBM applied twice a week for 4 weeks will be used as a control. The treatment will be performed on female participants aged between 45 and 60 years. After 4 weeks, evaluations of photographic images by specialists (Wrinkle Assessment Scale) as well as the quantitative analysis of the wrinkle size by the Image J software, the depth and width of wrinkles (assessment of face impressions by optical coherence tomography) and the level of Satisfaction with Facial Appearance Overall will be compared with data collected before the start of the study. All data will be analyzed statistically according to their distribution, seeking a level of statistical significance of 0.05.

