As previously mentioned, some studies have been evaluating the effects of PBM on facial rejuvenation, with the majority using red light.^[19–26]^ However, there is a high level of variability in the treatment parameters, in the frequency and duration of the sessions, and in the total time of application of the PBM, hence the need for controlled studies to define the ideal parameters. This study was concerned with comparing the effects of 2 regimes of application of PBM on facial rejuvenation.

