#### 2.1.3. Sample size calculation.

The sample size was calculated based on the primary outcome. The outcome considered was the classification of the Lemperle Wrinkle Assessment Scale (WAS).^[29]^ In the study by Sylvie Boisnic,^[30]^ the authors observed that the Lemperle score decreased in both groups after 12 weeks of treatment with a reduction of 1 (±0.7) point in the experimental group and 0.34 (±0.5) point in the placebo group and a statistically significant (*P* < .0002) change from baseline between the 2 groups after 8 weeks of treatment. This study was designed to detect a difference in scores between the groups, considering the mean and standard deviation of the study by Sylvie Boisnic,^[30]^ for the analysis of variance (ANOVA) with 3 groups and repeated measures, with significance level of 5% and power of 95%, with equal allocation for the three groups, requiring 24 participants per group, 72 in total. To control a possible loss, 50% can be added to the sample, with 36 participants per group, that is, 108 in total. The sample calculation was performed using the G-Power Version 3.1.9.4 program (Universität Kiel, Germany).

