#### 2.2.1. WAS.

The evaluation of wrinkles will be carried out in a standardized way using the WAS.^[29]^ This scale was developed and validated to quantify facial wrinkles based on predefined photographic models. To take photographs of the face, the participants will sign the image authorization term for use in the research and must be without any type of makeup. In a specific and reserved room, digitalized photographs of the face will be taken in the positions: front and 45 degrees right and left; with a Canon digital camera model SX510 HS 12.1 MP (Canon Do Brasil Indústria E Comércio | Ltda. São Paulo, SP, Brazil), using white LED lighting, turquoise blue background, 50 cm face distance, manual macro mode, a standard that will be followed in the photographs 30 days after the end of the treatment. The images obtained will be edited and standardized to be evaluated by the specialists according to the WAS.^[29]^ All images will be stored on a virtual disk which only the researcher will have access using a password. The images will be distributed later to the 3 plastic surgeons who will classify them according to the scale of wrinkles and photographic models pre-defined. Each evaluator will receive the same image of wrinkles, all at the end of the experiment. Each image should receive a score from 0 to 5 using the WAS as described previously.^[29,31]^ The data obtained will be grouped and the evolutionary comparison will be made according to the group of the patient under study.

To ensure homogeneity in the evaluation, an intra and interobserver agreement calculation will be performed before the sample is evaluated. Each specialist will receive 20 photographs of patients who did not participate in the study to classify facial wrinkles at any given time. After 7 days they will receive the same photographs and will need to classify the wrinkles again. The agreement index will be calculated for each evaluator and between the evaluators and an acceptable value of agreement must be above 70%.

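### The comparisons stated for the wrinkle score do not agree, and section 2.3 does not say that the group-by-time term of the repeated measures ANOVA decides

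*Protocol article*

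**What the plan says.** Section 2.1.3 bases the sample size on the primary outcome, the Lemperle Wrinkle Assessment Scale (WAS). Five places in the protocol article then bear on what is compared with what.

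- **Abstract, Methods and analysis.** The stated objective is to compare two application frequencies, with a simulated treatment group as control. The only sentence on how outcomes are compared lists the WAS, Image J, wrinkle depth and width, and satisfaction, and says that these, down to "the level of Satisfaction with Facial Appearance Overall will be compared with data collected before the start of the study".
- **Section 1, Introduction.** "This study was concerned with comparing the effects of 2 regimes of application of PBM on facial rejuvenation".
- **Section 2.1.3.** "This study was designed to detect a difference in scores between the groups". The inputs are "a reduction of 1 (±0.7) point in the experimental group and 0.34 (±0.5) point in the placebo group" from a cited study, and the method is given as "for the analysis of variance (ANOVA) with 3 groups and repeated measures".
- **Section 2.2.1.** For the WAS, "the evolutionary comparison will be made according to the group of the patient under study".
- **Section 2.3.** Numerical variables go into a repeated measures ANOVA, and Tukey's test follows if the groups differ. The section does not say whether the group, time or group-by-time term is meant.

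**The concern.** Three questions are in play: whether wrinkles changed from baseline, whether PBM beats sham, and whether one frequency beats the other. The same data can answer them differently. All three arms can improve from baseline while no arm differs from another, and the protocol's own planning figures have the placebo group improving.

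The ANOVA adds a second ambiguity. With one measurement before and one after treatment, its three terms test different things:

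- The time term is a before-after test pooled over arms, sham included.
- The group term compares arms on the average of baseline and follow-up, so randomised arms that start equal show only half of any treatment difference.
- The group-by-time term compares arms on change from baseline. Only this one isolates the treatment effect at full size.

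The condition in section 2.3 for going on to Tukey's test, a difference between groups, reads most literally as the group term.

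**Working it through.** **1. The plan's own figure.** Inputs from section 2.1.3: mean reductions 1.0 (SD 0.7) and 0.34 (SD 0.5), alpha 5% (taken as two-sided), power 95%, 24 per group.

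- Difference: 1.0 − 0.34 = 0.66.
- Pooled SD: √[(0.7² + 0.5²)/2] = √0.37 = 0.608.
- Standardised difference: 0.66/0.608 = 1.085.
- Two-sample t-test, noncentral t: power 0.949 at 23 and 0.957 at 24 per group.

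So 24 per group matches a two-group comparison of active with placebo on change. The named three-group method cannot be checked, because its effect size, within-person correlation and term are not given. A one-way ANOVA on change would need 21 per group if both regimens match the cited active arm, and 28 if one lies midway. No expected difference between regimens appears anywhere, so the question in the Introduction has no sizing input of its own.

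**2. What a before-after test would show in the sham arm.** Paired t-test, two-sided 5%, noncentrality (mean change/SD of change) × √n. For the first row at n = 24 this is (0.34/0.5) × √24 = 3.33, against a critical t of 2.07 on 23 degrees of freedom.

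| Assumed sham change | n = 24 | n = 36 |
|---|---|---|
| 0.34, SD 0.5 (section 2.1.3) | 0.89 | 0.98 |
| 0.34, SD 0.7 | 0.63 | 0.81 |
| 0.17, SD 0.5 (half the change) | 0.36 | 0.51 |

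If PBM did nothing and all three arms changed as in the first row, all three before-after tests would be significant with probability 0.8905³ = 0.71 at n = 24 and 0.9776³ = 0.93 at n = 36. A between-group test on change would be significant in about 5% of such trials.

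**3. Group term against group-by-time term.** Assumptions: both regimens reach the cited active change, baseline means are equal, the variance is the same at both visits, the pooled SD of change is 0.608, and the before-after correlation is ρ = 0.5.

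- The SD of change is σ√[2(1 − ρ)], so at ρ = 0.5 the SD at a single visit is σ = 0.608. The SD of the two-visit average is σ√[(1 + ρ)/2] = 0.608 × √0.75 = 0.527.
- With two arms equal and one different, the SD of the three means is the difference × √2/3.
- Group-by-time: f = 0.66 × 0.4714/0.608 = 0.511. Noncentrality is 72 × 0.511² = 18.8, and power at 24 per group is 0.97.
- Group: the difference on the average is 0.66/2 = 0.33, so f = 0.33 × 0.4714/0.527 = 0.295. Noncentrality is 72 × 0.295² = 6.3, and power is 0.58.
- At 36 per group the two powers are above 0.99 and 0.78.
- With the SD of change held at 0.608, power for the group term at 24 per group is 0.80 at ρ = 0.3 and 0.34 at ρ = 0.7. Power for group-by-time does not move.

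**The case against.** The strongest reply is that the methods do plan a between-group test. Section 2.1.3 is sized for one and section 2.3 describes one, while the abstract is a one-sentence summary that follows an objective naming the regimens and a sham control. The wording in section 2.2.1 fits change over time by group at least as well as a within-arm test. Tukey's procedure covers all three pairs with familywise control, and testing all pairs is a legitimate strategy. A statistical analysis plan that is not shown may name the deciding term.

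Most of this stands. A reader might infer from the abstract that the trial has no between-group analysis, or that the sponsor will claim efficacy from a paired test within an arm. The documents support neither: no section prescribes such a test or such a claim. A reader might also infer that the before-after reading would usually call the sham effective. That depends on a 12-week placebo change carrying over to a shorter schedule, and at half that change the probability is 0.36 to 0.51. Nor are these probabilities error rates to set against 5%, since a paired test that detects a real mean change is correct. The error would be to credit the change to light.

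Two things are left. The abstract, the Introduction and section 2.1.3 state different comparisons, and an unseen analysis plan cannot make the published text agree. Tukey's test governs the pairs once the ANOVA has been read, but it does not settle which term is to be read.

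**Conclusion.** The point holds as an inconsistency between the stated comparisons together with an unfixed ANOVA term. It is a clarity fault with real consequences, not a missing between-group analysis.

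Its size is conditional. On the protocol's planning figures, reading the group term instead of group-by-time would lower power at 24 per group from 0.97 to about 0.58, given a correlation of 0.5 and equally effective regimens. The sham-arm probabilities show how far a before-after reading could part from a between-group one. They rest on ±0.5 being the SD of change and on the cited placebo change carrying over, neither of which the documents establish.

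**What to change.** State in section 2.3: the deciding test on the WAS is the between-group difference in change from baseline, that is, the group-by-time term of the repeated measures ANOVA. The Tukey pairs already planned follow on change from baseline: each PBM regimen against sham, and one regimen against the other. Before-after changes within an arm are descriptive, shown with confidence intervals, and support no efficacy claim.

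Reword the comparison sentence in the abstract to match, and let the Introduction name both the comparison with sham and the comparison of regimens. No particular order of the pairs need be imposed.

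The cost is a few sentences, with no extra participants or data. The article describes the study as recruiting and has the photographs scored at the end of the experiment, so the rule can be fixed before results are seen. The small downside is that improvement within an arm can no longer be offered as evidence of efficacy.

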**Ethics and dissemination::**

This protocol was approved by the Research Ethics Committee of the Nove de Julho University (acceptance number: 4.365.565). This trial has been registered in ClinicalTrials.gov (ID: NCT04911140). This study is recruiting.

## 1. Introduction

Human skin aging results from the combination of biochemical, morphological, and physiological changes over time, genetic and epigenetic factors, and cumulative damage caused by external factors, including smoking, diet, severity, and most notably, ultraviolet radiation.^[1–6]^ These changes decrease the musculoskeletal support of the face, thus leading to loss of volume and changes in shape that can impact the quality of life, social relationships, and activities of individuals. Thus, preventive and corrective interventions are closely related not only to health but also to psychosocial well-being.^[7–9]^

The search for procedures to slow the aging process is increasing; limiting or hiding its effects on the skin and its appearance. The main surgical procedures for facial rejuvenation are facelift, rhinoplasty, otoplasty, and blepharoplasty. Facial lifting aims to improve facial and cervical aesthetics by suspending muscle compartments and skin giving the patient a more youthful appearance.^[10]^

In recent years, both dermatology and plastic surgery have given increasing importance to minimally invasive rejuvenation treatments capable of providing satisfactory results.^[11,12]^ However, even though they are minimally invasive, these procedures are not without complications, which can involve not only local pain, edema, and ecchymosis.^[13]^

On the other hand, photobiomodulation (PBM), which has also been used in facial rejuvenation, consists of the use of non-ionizing, non-thermal, and non-ablative light, without side effects and is capable of generating analgesic, anti-inflammatory and repairing results.^[14,15]^ PBM most commonly employs light (light amplification by stimulated emission of radiation [LASER] and light emitting diode [LED] devices) in the range of visible red and near-infrared (600–1100nm) to achieve desired therapeutic effects.^[16]^ Dosimetric parameters of PBM include wavelength, radiant energy and power, irradiance, and radiant exposure which are directly related to the ability of light to penetrate tissues and produce biological effects.^[14]^

The therapeutic effect of LEDs can be as efficient as that of LASERs as long as the same dosimetric application parameters are respected. These sources have advantages in the fact that they can be grouped for applications in larger areas and still bring security for home use.^[14,17,18]^

As previously mentioned, some studies have been evaluating the effects of PBM on facial rejuvenation, with the majority using red light.^[19–26]^ However, there is a high level of variability in the treatment parameters, in the frequency and duration of the sessions, and in the total time of application of the PBM, hence the need for controlled studies to define the ideal parameters. This study was concerned with comparing the effects of 2 regimes of application of PBM on facial rejuvenation.

## 2. Materials and methods

### 2.1. Study design

This randomized, controlled, blinded clinical trial was written according to the Standard Protocol Items: Recommendations for Interventional Trials checklist and following the Declaration of Helsinki. This protocol was approved by the Research Ethics Committee of the Nove de Julho University on October 27, 2020 (acceptance number: 4.365.565). This trial has been registered in ClinicalTrials.gov (ID: NCT04911140). This study is recruiting.

After a verbal and written explanation of the study, the participants who agree to take part in the research will sign the informed consent form. All participants will be seen at the clinic of specialties at Nove de Julho University - São Paulo, Brazil.

The patients and/or the public were not involved in the design, recruitment, and conduct of the study. Standard Protocol Items: Recommendations for Interventional Trials schedule of enrollment, interventions, and assessments according to Figure 1.

**Figure 1. F1:**
[figure not shown]
SPIRIT schedule of enrollment, interventions, and assessments. Pg 5. SPIRIT = Standard Protocol Items: Recommendations for Interventional Trials.

#### 2.1.1. Inclusion criteria.

A screening questionnaire with identification information of the participant will be applied, such as name, age, address, telephone, email, marital status, and education, in addition to a brief anamnesis on comorbidities, medications in use, and procedures performed on the face, among others. Only participants who meet the eligibility criteria will be included in the study such as female volunteers, aged 45 to 60 years, at menopause (at least 12 months without menstruation), and healthy.

In the same questionnaire, participants will be classified according to the skin phototype by the Fitzpatrick classification.^[27]^ The phototype of each participant will be identified, and only those that have a score will participate in the research, that is, phototypes from I to IV. The Glogau classification^[28]^ will also be part of the questionnaire, a categorization system for photo-damaged skin that estimates the level of skin damage. This system has been useful to assess levels of the dermo-epidermal lesion and fits the skin into four types. Only participants categorized as Glogau type II to IV will be part of the study.

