#### 2.1.4. Randomization.

After completing a questionnaire and being evaluated by the researcher for inclusion and exclusion criteria, a person not involved in the study will randomly distribute the participants among the three experimental groups using an online random sequence generator program (https://www.randomizer.org/tutorial/). After this, opaque envelopes, containing the generated number, will be sealed and will remain in a safe place until participants are recruited for the outpatient clinic. When the participant enters the clinic, the researcher will open the corresponding envelope and begin the specified treatment. Participants will be divided into 3 groups:

(Group 1) Application of PBM twice a week for 4 weeks;

(Group 2) Application of PBM three times a week for 4 weeks;

(Group 3) Application of simulated PBM twice a week for 4 weeks;

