## 3. Discussion

PBM, through the use of LEDs and LASERs, has shown good results in the treatment of wounds, increasing the formation of fibroblast cells, collagen synthesis, and reduction and control of inflammatory cells with a consequent increase in tissue formation.^[35]^ Recently, some studies have proposed the use of PBM for aesthetic medicine.^[36]^ The use of LED devices brings practicality and safety to applications and has also been evaluated for facial rejuvenation, mainly in the red wavelength.^[17]^ PBM is indicated for mild facial photoaging, fine wrinkles, skin damage, and texture changes. They are not indicated as replacement therapy for loss of volume, facial contour, sagging skin, or deep rhytids.^[25]^ However, dosimetric parameters, application frequencies, and total treatment time vary greatly.

In addition, the instruments used to evaluate the results are often subjective, highlighting the need for additional evaluations through more precise methodologies. This work described a randomized, controlled, double-blind clinical trial protocol based on the comparison of a treatment to be performed in 3 groups for 4 weeks: one group will receive the application of the red LED mask 3 times a week, another group will receive treatment 2 times a week and the control group will perform the simulated application of the LED mask twice a week. To increase participant compliance, a neutral face cream formulation was donated to be used by all patients at night during treatment.

The sample should be as homogeneous as possible to minimize individual biases, hence the importance of delimiting the age of participants between 45 and 60 years old, Glogau from 2 to 4, and who are in menopause. It is known that menopausal hypoestrogenism leads to changes in skin metabolism, such as changes in collagen fibers and reduced water content, favoring aging.^[37]^ Skin types II, III, and IV were chosen as inclusion criteria to standardize the melanin content of the participants, excluding the other phototypes I, V, and VI to reduce light absorption by melanin.^[38]^

Other important issues are that this protocol proposes a double-blind study and the randomization will be performed in blocks.

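### Glogau type spans three of four severity levels and is known before randomisation, but the protocol gives it no role in allocation or in the stated analysis

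*Protocol article*

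**What the plan says.** **Entry.** Protocol article, 2.1.1 Inclusion criteria, introduces the Glogau classification as "a categorization system for photo-damaged skin that estimates the level of skin damage", with four types, recorded in the screening questionnaire. It then sets the limit: "Only participants categorized as Glogau type II to IV will be part of the study". No upper limit on baseline wrinkle score or wrinkle depth is stated.

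**Reason given.** Section 3, Discussion, says "The sample should be as homogeneous as possible to minimize individual biases" and gives age 45 to 60, Glogau 2 to 4 and menopause as the means to that end.

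**Indication.** The same section says: "PBM is indicated for mild facial photoaging, fine wrinkles, skin damage, and texture changes". It continues: "They are not indicated as replacement therapy for loss of volume, facial contour, sagging skin, or deep rhytids".

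**Allocation.** Section 2.1.4, Randomization: "a person not involved in the study will randomly distribute the participants among the three experimental groups using an online random sequence generator program". The Discussion adds that "the randomization will be performed in blocks". Neither place names a stratification factor.

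**Analysis.** Section 2.3 compares numerical variables by repeated measures ANOVA with a Tukey post hoc test, and categorical variables by chi-square. It names no Glogau term, covariate or subgroup.

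**The concern.** Two things do not sit well together. First, a range that leaves out only one of four damage levels is offered as a way to make the sample homogeneous. The level left out is at the mild end, although the Discussion opens its list of indications with mild photoaging and fine wrinkles. Second, the variable that measures this spread is in hand before any envelope is opened, and the protocol makes no use of it.

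If change in wrinkle score depends on baseline severity, the mix of types adds variance to every comparison, and an uneven mix shifts the estimate in that one trial. The comparison most exposed is twice weekly against three times weekly. It is the trial's stated purpose, and its true difference may well be smaller than that of active treatment against sham. If women at the severe end did gain less, a small average effect would also be harder to interpret.

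**Working it through.** **1. The plan's own figure.** Section 2.1.3 gives reductions of 1 (SD 0.7) and 0.34 (SD 0.5), 5% significance, 95% power, 24 per group, raised by 50% to 36.

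- Difference = 1 − 0.34 = 0.66.
- Pooled SD = √((0.7² + 0.5²)/2) = √0.37 = 0.608.
- Standardised difference = 0.66/0.608 = 1.085.
- Two-sided two-sample t test (noncentral t): power is 94.9% at 23 per group and 95.7% at 24.

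So 24 is reproduced as a pairwise comparison of active treatment with sham, and 24 × 1.5 = 36. The sample size is not in dispute here. It does assume the full 0.66 on average in the women enrolled.

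**2. Chance imbalance in severity.** The protocol gives no expected split by type, so a severe share p (for example types III and IV together) is assumed at 30 to 50%. Without stratification, the number of severe women in each arm is approximately binomial(n, p). A gap of at least 20 percentage points means at least 5 women in 24, or at least 8 in 36.

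| n per arm | p | two given arms | some pair of the three |
|---|---|---|---|
| 24 | 30% | 15.5% | 33% |
| 24 | 50% | 19.3% | 39% |
| 36 | 30% | 5.3% | 13% |
| 36 | 50% | 7.6% | 18% |

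Blocks without strata equalise arm sizes but not the severity mix, so they do not remove this.

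**3. What such a gap could do.** Take the extreme assumption that severe women gain nothing over sham and the others gain 0.66. A gap of 5 in 24 between the two active arms would then shift their contrast by (5/24) × 0.66 = 0.14 points. With weaker dependence on severity the shift shrinks in proportion, and with none it is zero.

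**4. Dilution, as illustration only.** Let a share f of women gain nothing over sham. The protocol gives no value for f; 10 to 30% is assumed.

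- Difference = 0.66(1 − f).
- Active-arm variance = 0.49 + f(1 − f) × 0.66².
- SD for the comparison = √((active-arm variance + 0.25)/2).

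| f | difference | SD | power, 24 per arm | power, 36 per arm |
|---|---|---|---|---|
| 0 | 0.660 | 0.608 | 95.7% | 99.5% |
| 10% | 0.594 | 0.624 | 89.7% | 97.8% |
| 20% | 0.528 | 0.636 | 80.3% | 93.5% |
| 30% | 0.462 | 0.645 | 68.1% | 85.0% |

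The column for 36 applies if nobody is lost. The column for 24 applies if the whole allowance for loss is used up.

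**The case against.** A reader might infer that the protocol enrols women it expects not to respond. The text does not support that. The list of indications also includes skin damage, which is what the Glogau scale is said to measure, and texture changes. The sentence on deep rhytids speaks of replacement therapy, which can mean that light treatment does not stand in for other procedures, not that such skin will not respond. No section ties a Glogau type to deep rhytids or predicts response by type. Requiring some damage at entry also suits the endpoints: the tomography needs a visible wrinkle to measure, and a score near 0 on a 0 to 5 scale has little room to fall. All of this stands.

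A reader might also infer that the comparison is biased. It is not, in the systematic sense: randomisation balances severity on average. The before-after analysis also removes stable differences in level between women. What it does not remove is any dependence of the change itself on severity.

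The dilution table rests on an assumed share and on the extreme case of no gain at all. The severity mix of the study that supplied the planning figures is not given either, so some dilution may already be in the 0.66. The table shows sensitivity and is not an estimate.

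Last, covariates and subgroups may be set out in an analysis plan that is not shown, so their absence from section 2.3 is the weaker half of the point. Stratification is different. It has to be fixed before allocation, and both descriptions of the randomisation omit it.

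**Conclusion.** The point holds as a worthwhile and inexpensive improvement, together with a wording inconsistency to resolve. It does not establish an error that undermines the trial.

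Three things are firm. The range covers three of four types, which sits badly with the homogeneity claim. There is a tension at the severe end with the Discussion's statement on indication. And a severity measure known before randomisation has no stated role in allocation.

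The consequence is added variance and a risk of chance imbalance. A gap of 20 points or more between two given arms has a probability of about 16 to 19% at 24 per arm and 5 to 8% at 36, for an assumed severe share of 30 to 50%. It matters only so far as change depends on severity, which the protocol does not say. Any loss of power is illustrative: for an assumed 10 to 30% of women with no gain over sham, pairwise power is 90 to 68% at 24 per arm and 98 to 85% at 36.

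**What to change.** - **Allocation.** Stratify the blocked randomisation by Glogau type, for example II versus III–IV, for participants still to be enrolled, and record the date of the change, since the trial is described as recruiting.
- **Analysis.** Include Glogau type and its interaction with time in the repeated measures model. The interaction is needed because a main effect alone does not adjust the comparison of change between groups. Using Glogau type as a covariate in an analysis of change from baseline is equivalent.
- **Reporting.** Show the effect by Glogau type as exploratory only. Do not restrict the main conclusion to whichever type shows an effect, because the subgroups are too small for that.
- **Wording.** The sponsor should reconcile the eligibility range in 2.1.1 and the homogeneity claim in the Discussion with the Discussion's statement on indication. Which types to admit is the sponsor's decision.

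**Cost.** Two sets of envelopes instead of one, one or two extra model terms, and a documented change of allocation during recruitment. No extra participants, visits or data are needed. Estimates by type will be imprecise, and splitting at II versus III–IV does not isolate type IV.
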